# Vocal-cord Only vs. Complete Laryngeal radiation (VOCAL): a randomized multicentric Bayesian phase II trial

**DOI:** 10.1186/s12885-021-08195-8

**Published:** 2021-04-22

**Keywords:** Glottic cancer, Larynx, Radiotherapy, Vocal cord, Local control

## Abstract

**Background:**

Radiotherapy, along with laser surgery, is considered a standard treatment option for patients with early glottic squamous cell cancer (SCC). Historically, patients have received complete larynx radiotherapy (CL-RT) due to fear of swallowing and respiratory laryngeal motion and this remains the standard approach in many academic institutions. Local control (LC) rates with CL-RT have been excellent, however this treatment can carry significant toxicities include adverse voice and swallowing outcomes, along with increased long-term risk of cerebrovascular morbidity. A recent retrospective study reported improved voice quality and similar local control outcomes with focused vocal cord radiotherapy (VC-RT) compared to CL-RT. There is currently no prospective evidence on the safety of VC-RT. The primary objective of this Bayesian Phase II trial is to compare the LC of VC-RT to that of CL-RT in patients with T1N0 glottic SCC.

**Methods:**

One hundred and fifty-five patients with T1a-b N0 SCC of the true vocal cords that are n ot candidate or declined laser surgery, will be randomized in a 1:3 ratio the control arm (CL-RT) and the experimental arm (VC-RT). Randomisation will be stratified by tumor stage (T1a/T1b) and by site (each site will be allowed to select one preferred radiation dose regimen, to be used in both arms). CL-RT volumes will correspond to the conventional RT volumes, with the planning target volume extending from the top of thyroid cartilage lamina superiorly to the bottom of the cricoid inferiorly. VC-RT volumes will include the involved vocal cord(s) and a margin accounting for respiration and set-up uncertainty. The primary endpoint will be LC at 2-years, while secondary endpoints will include patient-reported outcomes (voice impairment, dysphagia and symptom burden), acute and late toxicity radiation-induced toxicity, overall survival, progression free survival, as well as an optional component of acoustic and objective measures of voice analysis using the Consensus Auditory-Perceptual Evaluation of Voice.

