## Methods/design

### Study objectives

The objective of this trial is to assess the efficacy and safety of VC-RT, compared to CL-RT, in T1N0 glottic squamous cell carcinoma.

Primary endpoint:
Local control at 2-year after the end of RT.

*Local control will be defined as absence of biopsy proven recurrence within the larynx.*

Secondary endpoints:
Patient-reported outcomes including dysphagia, voice impairment, and symptom burden.Acute and late toxicity radiation-induced toxicityOS and progression free survival (PFS)Acoustic and objective measures of voice analysis using the Consensus Auditory-Perceptual Evaluation of Voice.

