### Study assessments

There will be evaluation immediately post-treatment, as well as at 6, 12 and 24 months post-treatment as part of the study. Other follow-ups will be as per institution standard of care, but suggested schedule of assessments detailed in Table 1 is encouraged.Alternate follow-ups between the head and neck surgeon and the radiation oncologist will be mandatory.Physical examination will involve flexible laryngoscopy or/and videostrobe or/and mirror examination with adequate visualisation of vocal cords.Clinical follow-up will involve documentation of LC and survival status as well as reporting of CTCAE V4.03 toxicities.Patients will be asked to fill patient-reported outcome questionnaires at baseline and at each visit, as detailed in Table 1. The questionnaires will be administered in the following order: VHI-10, MDADI and MDASI-HN. The questionnaires could be filled in paper format, or online using the anonymized CASTOR EDC system. The questionnaires will not be reviewed during the study and will be analysed only at the pre-specified timepoints.There will be an *optional* assessment of acoustic and objective measures of voice analysis by a speech pathologist at baseline, immediately post-treatment and at 6 months post treatment. The assessments will consist in a digital recording of a standard oral reading passage and a short monologue, which would later be analyzed for specific acoustic variables and microacoustic measures of the cycle-to-cycle variation of acoustic parameters (in frequency and intensity domains). The voice quality will be graded as per then GRBAS scale (grade, roughness, breathiness, asthenia, strain).

**Table 1 Tab1:** Suggested Schedule of Assessments

	Pre-RT	End of RT	2mo^a^	6mo	12 mo	24 mo	36mo^a^	48mo^a^	60mo^a^
History (including TIA or stroke) & physical exam (including laryngoscopy)	x	x	x	x	x	x	x	x	x
Side effects			x	x	x	x	x	x	x
TSH^a^	x				x	x	x	x	x
Questionnaire VHI −10	x	x	x	x	x	x	x	x	x
Questionnaire MDADI and MDASI-HN	x	x	x	x	x	x	x	x	x

*RT* Radiotherapy, *Mo* months

^a^Optional assessments

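### Acute toxicity is a secondary endpoint, but Table 1 schedules no side-effect grade before or at the end of radiotherapy and conflicts with the text; the perceptual voice scale is also named inconsistently

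*Protocol article*

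**What the plan says.** Both the Abstract (Methods) and Study objectives make acute and late toxicity a secondary endpoint; the Abstract's wording is "acute and late toxicity radiation-induced toxicity".

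Study assessments fixes the study visits: "There will be evaluation immediately post-treatment, as well as at 6, 12 and 24 months post-treatment as part of the study". Other visits follow local practice, with the "suggested schedule of assessments" in Table 1 encouraged. On toxicity the text says: "Clinical follow-up will involve documentation of LC and survival status as well as reporting of CTCAE V4.03 toxicities". That sentence names no visit.

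In Table 1 the Side effects row is empty at Pre-RT and End of RT and marked at 2, 6, 12, 24, 36, 48 and 60 months. The 2-, 36-, 48- and 60-month columns carry the footnote "Optional assessments".

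For voice, Study objectives lists "Acoustic and objective measures of voice analysis using the Consensus Auditory-Perceptual Evaluation of Voice", and the Abstract calls this an "optional component of acoustic and objective measures of voice analysis using the Consensus Auditory-Perceptual Evaluation of Voice". Study assessments, where the procedure is described, says instead: "The voice quality will be graded as per then GRBAS scale".

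**The concern.** Lower acute and chronic toxicity is part of the case for vocal-cord radiotherapy in the Background (Vocal-cord only irradiation), and the Analytic plan compares toxicity between arms with a chi-squared or Fisher's exact test. That comparison needs grades taken at the same times in both arms, with at least one while acute effects are present. A site that works from Table 1 would first be sure to grade side effects at 6 months. It would also have no pre-treatment grade against which to judge a later one, in a disease that can itself impair the voice. Grades missed at these visits cannot be reliably reconstructed afterwards.

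The voice point is smaller: the endpoint and the procedure name different perceptual scales, so it is unclear which rating is to be reported.

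**Working it through.** There is no figure to reproduce; the check sets the table against the text.

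**Step 1: Table 1, row by row.** All rows have nine columns. The Side effects row against the history and examination row:

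| Visit | Optional column? | History and examination | Side effects |
|---|---|---|---|
| Pre-RT | no | x | blank |
| End of RT | no | x | blank |
| 2 months | yes | x | x |
| 6 months | no | x | x |
| 12 months | no | x | x |
| 24 months | no | x | x |
| 36 months | yes | x | x |
| 48 months | yes | x | x |
| 60 months | yes | x | x |

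Side-effect entries: 9 − 2 = 7, of which 4 are optional, leaving 7 − 4 = 3 non-optional entries (6, 12 and 24 months). Non-optional visits with an examination: 9 − 4 = 5. So 5 − 3 = 2 non-optional visits have an examination but no side-effect grade, and these are the baseline and end-of-treatment visits.

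The blanks do not look like a fault of text extraction. The other rows keep their columns: TSH, for example, is marked at Pre-RT and then from 12 months. The questionnaire rows are marked at both visits where Side effects is blank.

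**Step 2: the text.** The visits it makes part of the study (immediately after treatment, 6, 12 and 24 months) match the non-optional post-treatment columns of Table 1. Text and table therefore agree on when patients are seen. The CTCAE sentence applies to clinical follow-up and can be read in two ways:

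- *Follow-up includes the immediate post-treatment evaluation.* A grade is then due at end of RT, and the blank cell in Table 1 contradicts the text.
- *Follow-up means the later visits.* The text then agrees with Table 1, and an acute grade exists only where a site holds the optional 2-month visit.

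On neither reading is a pre-treatment grade scheduled: the text speaks of follow-up, and the table is blank at Pre-RT.

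**Step 3: voice.** The Abstract and Study objectives name the Consensus Auditory-Perceptual Evaluation of Voice. Study assessments names GRBAS and does not mention the other scale, and only GRBAS is in the abbreviation list.

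**The case against.** The best defence is that the text governs. An evaluation immediately after treatment is part of the study, CTCAE reporting belongs to clinical follow-up, and Table 1 is only a suggestion, so a blank cell need not override it. This stands as far as it goes. A reader might infer that acute toxicity cannot be obtained at all, and the document does not support that: the text can be read as collecting it at end of RT, and the optional 2-month visit also records side effects. What remains is that the only visit-by-visit schedule says otherwise, and that the defence does not supply a baseline grade.

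Second, early symptoms are measured in another way. VHI-10, MDADI and MDASI-HN are scheduled at baseline and at end of RT. Study design and Statistical considerations give voice, dysphagia and quality of life (Study design adds survival) as the purpose of randomisation, and do not name clinician-graded toxicity. This lowers the stakes. Patient-reported scores are still not CTCAE grades, and toxicity is a separate listed endpoint with its own planned test.

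Third, it is tempting to say that the missing baseline biases the comparison. The arms are randomised and stratified by site, so pre-existing hoarseness or uneven collection should not systematically favour one arm. The likely loss is completeness, precision and some dilution of a difference.

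Fourth, a reader might infer that the voice endpoint would have no data. It would: acoustic measures come from the digital recordings, and nothing prevents those recordings from being rated later on the scale that the endpoint names. The component is optional, and only the name of the perceptual scale is inconsistent.

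**Conclusion.** The point holds in a limited form. The visit schedule does not secure the acute part of the toxicity endpoint: two of the five non-optional visits in Table 1, baseline and end of RT, have no side-effect entry, and the first non-optional entry is at 6 months. Text and table conflict if follow-up is taken to include the post-treatment evaluation. If it is not, acute grades depend on an optional visit. Under the second reading, none of the 155 patients (39 CL-RT, 116 VC-RT) has an assured grade between randomisation and 6 months after treatment; under the first, an end-of-RT grade is due but a baseline grade is not. The loss of precision cannot be computed, because the document does not say how many sites will hold the 2-month visit; the arm with 39 patients has the least to spare.

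This assumes that Table 1 was extracted as printed, which the alignment of its other rows supports. The voice-scale mismatch is a minor inconsistency of wording. Neither matter touches local control at 2 years, the sample size or the interim stopping rule.

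**What to change.** Mark Side effects (CTCAE v4.03) at Pre-RT and End of RT in Table 1, and have the CTCAE sentence in Study assessments name the same visits. Report acute toxicity from the End of RT grade, adding the 2-month grade where that visit takes place, and report late toxicity relative to the baseline grade. The cost is one extra CRF page at two visits where history and examination already take place.

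Separately, name one perceptual voice scale in the Abstract, Study objectives and Study assessments. This is a wording change only, and the acoustic measures stay as they are.

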**Discussion:**

This study would constitute the first prospective evidence on the efficacy and safety of VC-RT in early glottic cancer. If positive, this study would result in the adoption of VC-RT as standard approach in early glottic cancer.

**Trial registration:**

ClinicalTrials.gov Identifier: NCT03759431

Registration date: November 30, 2018

**Supplementary Information:**

The online version contains supplementary material available at 10.1186/s12885-021-08195-8.

## Background

### Role of radiotherapy in early glottic cancer

Each year, over 150,000 new cases of laryngeal cancer are diagnosed worldwide [1] and over a thousand new cases are diagnosed in Canada [2]. Treatment options for early stage laryngeal cancer (T1–2N0) include transoral endoscopic microsurgery [3–5], radical radiotherapy (RT) [6–9] and, in rare cases, partial laryngectomy via open surgery [10–12]. Whereas endoscopic microsurgery (with or without laser) typically involves resection of only the tumor-bearing vocal cord with a narrow 1–2 mm margin, current standard RT involves irradiation of the entire larynx [13–15]. Although prospective evidence comparing RT to surgery is lacking, both treatment options were reported to have equivalent oncological outcomes in terms of local control (LC) and overall survival (OS) in several meta-analysis [16–18] and systematic reviews [19–23]. Radical RT outcomes for early glottic cancer are excellent with reported 5-year LC rates varying between 85 and 95% and 5-year OS exceeding 90% [6–8, 24, 25]. Although it is often suggested that RT is associated with better voice preservation compared to surgery, notably in larger tumors and tumors involving the anterior commissure [26], this remains controversial [19]. In a first meta-analysis including 8 retrospective cohort studies, although 2 studies reported improved voice preservation with RT, pooled results showed similar voice outcomes between transoral laser surgery and RT in T1 glottic cancers [27]. In a more recent meta-analysis including 14 studies and comparing outcomes of surgery vs. RT for T1 glottis cancers, while subjective voice assessments were comparable, RT was associated with improved maximum phonation time and decreased fundamental frequency [28]. Selection of optimal treatment modality currently involves institutional expertise and elicitation of patient preferences, and although substantiated by debatable evidence, also takes into account factors such as tumor size, location and histology [29–31]. In a recent prospective study on the choice of treatment in patients with T1–2N0 glottic cancer, it was reported while 51% of patients are oriented directly towards RT by the medical team (i.e. deemed not suitable for surgery), a third of patients offered either transoral laser surgery or RT opted for RT [32].

### Toxicities of complete larynx radiotherapy

Despite good LC, a substantial number of patients treated with radical RT experience persistent voice impairment after treatment [33]. Several studies have reported mild-to-moderate voice impairments after early glottic cancer RT in the acute, subacute and chronic settings [27, 34–36]. There is currently limited data on threshold doses for functional voice preservation and, in the context of current RT fields, this has been of little pertinence considering that the entire larynx would receive the full dose, leaving little room for organs at risk sparing. Dornfeld et al. [37] found a strong correlation between quality of speech and doses to various structures of the glottic and supraglottic larynx as well as the pharyngeal walls. Available dose-volume data suggest that mean dose to the larynx above 45 Gy and mean dose to the non-involved vocal cord above 50 Gy are predictors of grade ≥ 2 laryngeal oedema and worse voice outcomes [38, 39].

Other common toxicities of larynx RT for early glottic cancer include increased risk of carotid artery stenosis and hypothyroidism. Cerebrovascular morbidity from carotid artery stenosis has been documented in several studies in the setting of conventional RT [40–42]. In a recent SEER-database study, RT for treatment of early glottic cancer was associated with an increased risk of mortality due to cerebrovascular events in comparison to surgery [42]. Doses to the carotids between 35 and 50 Gy have been associated with carotid vessels wall thickening [43]. In addition, rates of radiation-induced hypothyroidism vary between 13 and 47% [35, 44], with highest frequency at 1 year after treatment. Other severe toxicities of larynx RT include less than 1% risk of permanent tracheostomy due persistent laryngeal oedema and loss of functional larynx [35, 45] and less than 1% risk of persistent mild or moderate dysphagia [46]. Importantly, laryngeal cancer patients have 22% risk of developing a secondary malignancy, with the wide majority originating from the upper aero-digestive tract [47]. In this context, their previous history of complete larynx RT limits their future therapeutic options.

### Complete larynx radiation field and larynx motion

The historical standard for early glottic cancer remains the use of 3D-conformal radiotherapy, most commonly using lateral opposing fields, with field size of 5 × 5 cm^2^ to 6 × 6 cm^2^ [13, 14] centered on the thyroid cartilage. Typically, the superior, posterior, inferior and anterior borders of the field are 0.5–1.0 cm above the thyroid notch, 1 cm behind the thyroid cartilage, below the cricoid and 1 cm beyond the patient’s external contour, respectively [13]. Although the use of intensity modulated radiotherapy (IMRT) for early glottic cancer remains controversial, several institutions have adopted carotid-sparing IMRT planning [15, 48, 49]. Clinical outcomes from complete larynx IMRT was published by the Memorial Sloan-Kettering Cancer Center and showed excellent 3 years LC [15]. The margins used in complete larynx IMRT remain conservative because of fear of geographical miss associated with internal motion of the larynx such as swallowing or breathing.

Although swallowing motion is associated with large larynx excursion up to 2 cm in the superior direction [50–53], swallowing motion was reported to be rare, rapid and easily suppressed by patients, and is therefore considered to have negligible impact on RT dose delivery [50, 53–56]. Although precaution should be taken to ensure that the planning CT is not acquired while the patient is swallowing (to avoid a risk of systematic error throughout treatment), additional margins to account for swallowing motion appear unnecessary [50]. On the other hand, respiratory motion in the order of several millimetres has also been described [54, 55]. Respiratory motion reaching 6 mm in the superior-inferior direction and 2 mm in the antero-posterior direction has previously been described [50]. Such intra-fraction motion cannot be addressed by means of daily image guidance and can be associated with a risk of tumor miss in the context of tighter treatment margin. In addition, occurrence of a larynx shift in relation to the vertebral structures, potentially resulting from anatomical changes over time or set-up reproducibility, has also been described [50, 57]. The latter finding stresses the importance of daily imaging with laryngeal match rather than bone match if tight margins are considered.

### Vocal-cord only irradiation

In recent years, increasing interest in reducing RT treatment volumes has emerged, with the objective of reducing toxicity while maintaining LC. In fact, in the era of IMRT and image-guided radiotherapy (IGRT), it is appealing to mirror surgical approaches and evaluate vocal-cord radiotherapy (VC-RT). Focal vocal cord RT for T1N0 glottic cancer has been assessed in dosimetric studies which confirmed adequate target volume coverage [58], homogeneity of planning target volume (PTV) coverage [50], as well as sparing of various laryngeal structures (including the contralateral vocal cord and arytenoid), the carotids and thyroid gland compared to conventional RT [50, 59, 60]. The group from Erasmus Medical Center Cancer has reported clinical outcomes from a retrospective analysis of 30 patients with T1aN0 glottic cancer treated with VC-RT [35]. They reported excellent 2 year LC of 100% as well as lower rates of acute toxicities and improved voice outcomes compared to a similar cohort of patients treated with CL-RT [35]. In fact, VC-RT was associated with clinically significant voice preservation compared to CL-RT immediately after RT, at 6–12 weeks and at 6–12-18 months after RT [36]. By maximally avoiding structures involved in voice preservation, VC-RT has the potential to reduce the rate and severity of acute and chronic toxicities and minimize voice impairment, while maintaining current excellent local control rates. While some institutions have adopted a partial larynx RT approach in early glottic cancer, there is currently no prospective evidence on efficacy or safety of VC-RT and many academic institutions continue to consider treating the entire larynx as standard of care. The hypothesis of the current phase II study is that VC-RT would lead to non-inferior LC compared to historical outcomes of CL-RT in patients with T1N0 glottic cancer.

## Methods/design

### Study objectives

The objective of this trial is to assess the efficacy and safety of VC-RT, compared to CL-RT, in T1N0 glottic squamous cell carcinoma.

Primary endpoint:
Local control at 2-year after the end of RT.

*Local control will be defined as absence of biopsy proven recurrence within the larynx.*

Secondary endpoints:
Patient-reported outcomes including dysphagia, voice impairment, and symptom burden.Acute and late toxicity radiation-induced toxicityOS and progression free survival (PFS)Acoustic and objective measures of voice analysis using the Consensus Auditory-Perceptual Evaluation of Voice.

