### Statistical considerations

According to previous experience, expected LC after CL-RT is estimated to be 92% [6, 8]. Assuming a non-inferiority margin of 8%, if LC in the VC-RT arm is ≥84% at 2-years, we will deem the VC-RT arm acceptable. With a sample size of 111 patients, over 82% power will detect a margin difference of 8%, at a target significance level of 0.05 using a one-sided, exact binomial test (NCSS-PASS 2005). The purpose of the randomization will be to generate currently unavailable data on secondary outcomes of voice impairment, dysphagia and quality of life in the CL-RT arm. Considering a 5% attrition rate, 155 patients will be randomized in a 1:3 ratio to CL-RT (39 patients) and VC-RT (116 patients) arms. Patients will be stratified by stage (T1a/T1b) and by institution.

An interim analysis will be conducted when 55 patients have a minimal follow-up of 6 months. We will monitor the efficacy endpoint using the Bayesian optimal phase 2 (BOP2) design [62]. Specifically, let *n* denote the interim sample size and *N* denote the maximum sample size. Let *p*_*eff*_ denote the probability of efficacy (response rate) and define the null hypothesis *H*_0_ : *p*_*eff*_ < 0.84, representing that the treatment is inefficacious. We will stop enrolling patients and claim that the treatment is not promising if
$$ \mathit{\Pr}\left({p}_{eff}\ge 0.84\mid data\right)<\lambda {\left(\frac{n}{N}\right)}^{\alpha }, $$where *λ* =0.95 and *α* =1 are design parameters optimized to minimize the chance of incorrectly claiming that an efficacious treatment is not promising (i.e., type II error) under the alternative hypothesis *H*_1_ : *p*_*eff*_ = 0.92, while controlling the type I error rate at 0.05 (i.e., the chance of incorrectly claiming that an inefficacious treatment is promising is no more than 5%). Assuming a Beta (0.84,0.16) prior distribution for *p*_*eff*_, if more than 10 patients among the 55 patients develop recurrences, the trial will be stopped in the interim analysis. Otherwise, the trial will be continued.

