### Analytic plan

A Bayesian regression model [63, 64] will be used to compare the LC between the VC-RT and CL-RT arms at 2 years. The LC and OS time will be defined from end of RT date. The following recurrences will be considered LC: in field, field margin and within larynx. Local recurrences will be biopsy-proven when possible. Competing events will include local recurrence, regional/distant recurrence and death prior to recurrence. LC will be estimated using both competing risk and Kaplan -Meier (KM) analysis. The analyses will be conducted using SAS and R software. A Cox multivariable regression analysis will be used to determine factors predictive of LC, PFS and OS. Chi-squared test or Fisher’s exact test will be used to compare the difference in toxicity between arms. For the secondary endpoints of patient-reported outcomes (VHI-10, MDADI and MDASI-HN), trajectory trends of scores between/among arms over time will be explored using a generalized linear mixed model with a random effect of time. Appropriate adjustments for covariates will be considered.

There will be two planned analysis: 1) an interim analysis and, 2) a final analysis. The interim analysis will be done after 55 patients on the experimental arm have a minimum follow-up of 6 months. A short follow-up time of 6 months was chosen for the interim analysis for safety (i.e. for early detection of local recurrence trends). The trial may be interrupted early if VC-RT is deemed not promising on interim analysis. The final analysis will performed 2 years after accrual is completed.

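### Local control, the primary endpoint, is defined in two incompatible ways, and local recurrence is listed as a competing event to itself

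*Protocol article*

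**What the plan says.** All references are to the protocol article.

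- **Study objectives.** The primary endpoint is "Local control at 2-year after the end of RT". Its definition follows: "Local control will be defined as absence of biopsy proven recurrence within the larynx". Failure therefore needs both histological proof and a laryngeal site.
- **Analytic plan, site.** "The following recurrences will be considered LC: in field, field margin and within larynx".
- **Analytic plan, proof.** "Local recurrences will be biopsy-proven when possible".
- **Analytic plan, competing events.** "Competing events will include local recurrence, regional/distant recurrence and death prior to recurrence".
- **Analytic plan, estimators.** "LC will be estimated using both competing risk and Kaplan -Meier (KM) analysis".
- **Statistical considerations, decision.** "Assuming a non-inferiority margin of 8%, if LC in the VC-RT arm is ≥84% at 2-years, we will deem the VC-RT arm acceptable". The sample size of 111 comes from a one-sided exact binomial test at 0.05, with 84% against 92% and a stated power of over 82%.

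**The concern.** The two sections disagree on what a local failure is, in two respects.

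- **Proof.** Biopsy is a condition of failure in Study objectives and a preference in Analytic plan.
- **Site.** Study objectives is confined to the larynx. Analytic plan adds in-field and field-margin recurrence.

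Two further sentences in Analytic plan cannot be applied as written. One calls recurrences local control, where local failure must be meant. The other makes the event of interest compete with itself.

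The primary decision rests on a small count of failures. If the definition is chosen after the recurrences are known, the choice can settle the result, and the narrower definition can only favour VC-RT. The interim stopping rule (more than 10 recurrences among 55 patients) depends on the same count and does not say which definition applies.

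**Working it through.** **1. The two definitions are nested.** A biopsy-proven recurrence within the larynx counts under both sections. The classifications compare as follows:

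| Recurrence | Study objectives | Analytic plan |
|---|---|---|
| In larynx, biopsy-proven | failure | failure |
| In larynx, biopsy not possible | local control | failure |
| Outside larynx, in field or at field margin | local control | failure |

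The Study objectives count can never exceed the Analytic plan count, so the disagreement runs in one direction.

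**2. Reproducing the plan's power.** Inputs from Statistical considerations: n = 111, unacceptable local control 0.84, expected local control 0.92, one-sided 0.05, exact binomial. Let X be the number of failures.

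- P(X ≤ 11 | 111, 0.16) = 0.0464, and P(X ≤ 12 | 111, 0.16) = 0.0818. The test therefore accepts at 11 failures or fewer, that is, 100 or more of 111 controlled.
- Power = P(X ≤ 11 | 111, 0.08) = 0.823, which agrees with the stated figure of over 82%.

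The article does not print the cut-off of 11; it follows from the stated inputs. One patient is 1/111 = 0.9 percentage point of local control.

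**3. Effect of uncounted failures.** Let f be the share of true local failures that are never biopsied and so count as controlled. The article gives no value, so f is an assumption. At true local control of 84%, the expected number of true failures is 111 × 0.16 = 17.8. The apparent failure rate is 0.16 × (1 − f), and the false-acceptance probability is P(X ≤ 11 | 111, 0.16 × (1 − f)).

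| f (assumed) | Failures uncounted (17.76 × f) | Apparent local control | False acceptance |
|---|---|---|---|
| 0 | 0 | 84.0% | 4.6% |
| 5% | 0.9 | 84.8% | 7.2% |
| 10% | 1.8 | 85.6% | 10.9% |
| 20% | 3.6 | 87.2% | 22.5% |

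**4. How often one or two patients decide.** Moving one or two patients from failure to control reverses a rejection only if the full count is 12 or 13.

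- True local control 84%: P(12) + P(13) = 0.035 + 0.051 = 0.087.
- True local control 92%: P(12) + P(13) = 0.070 + 0.047 = 0.117.

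**5. Competing events.** A cumulative incidence needs one event of interest and a separate set of events that preclude it or end follow-up for it. With local recurrence in the second set, nothing is left in the first.

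How death is handled matters little. With constant hazards, 92% local control and an assumed 96% survival at 2 years, the cumulative incidence of local failure is 7.84%, against 8.00% for one minus Kaplan-Meier. The difference is about 0.2 point.

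**The case against.** **These are drafting slips.** No analyst could run a competing-risk analysis with the event of interest as its own competitor, and the Analytic plan elsewhere makes clear that local recurrences are the events. That is fair for the competing-event list and for the label of local control, and both need only a word or two. It does not cover the biopsy conflict, where each version is workable and they give different counts. A reader might infer that the list would censor the failures. The text does not support that: a competing event is not simply censored, and the literal sentence leaves the estimand undefined rather than biased in a known direction.

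**Unbiopsied recurrence should be rare.** The Analytic plan asks for biopsy whenever it can be done, physical examination must visualise the cords, and salvage is often total laryngectomy. This stands as a limit on size. The 5% row may be nearer the truth than the 20% row, and the article cannot settle it.

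**Biopsy proof also protects against false failures.** The Background describes laryngeal oedema after radiotherapy, and a clinical or radiological diagnosis can be wrong. This stands too. Which definition should be primary is a choice; the defect is that the article makes two.

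**The fields differ by arm.** A reader might infer that in-field and field-margin sites bias the primary comparison. They do not touch it, because VC-RT is judged against a fixed historical benchmark. Any laryngeal recurrence also counts in both arms under the Analytic plan, whatever the field. Only the secondary between-arm regression could be affected, and only by recurrences outside the larynx, for which no frequency is given.

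**Regional or distant recurrence as a competing event.** A reader might call this an error. It is a recognised first-failure approach and defensible. The article does not describe follow-up for laryngeal recurrence after such a relapse, so it cannot be shown to be wrong here.

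**Conclusion.** The point holds. The primary endpoint has two definitions that differ on proof and on site, no part of the article reconciles them, and two sentences of the Analytic plan are wrong as written.

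The size is conditional. If 5% to 20% of true failures went uncounted, the nominal 4.6% false-acceptance risk would become 7.2% to 22.5%. Those shares are assumptions, and the calculation supposes no false-positive failures. It is tempting to say that one or two reclassified patients would reverse the trial. That is true only near the boundary: a full count of 12 or 13 has probability of about 9% at 84% local control and about 12% at 92%, and the reclassified patients must also be among those failures.

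The stated sample size and power reproduce. The correction is needed because it concerns the primary endpoint and prevents a choice of definition after the data are seen.

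**What to change.** Before results are known:

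1. Use one definition of local failure in Study objectives and Analytic plan, for both the interim and the final count: recurrence anatomically within the larynx, either biopsy-proven or, where biopsy was not possible, diagnosed clinically or radiologically and recorded as such.
2. Report biopsy-proven failure only as a sensitivity analysis.
3. In the Analytic plan, replace the label of local control for these recurrences with local failure.
4. Name local recurrence as the event of interest and remove it from the competing events. Keep death without local failure as a competing event, and state whether regional or distant recurrence is intended as one.

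The cost is wording in the protocol and analysis plan, with no change to sample size. One or two more events may count against VC-RT. Some clinical diagnoses may be false failures; the sensitivity analysis shows how far the conclusion depends on them.
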